#### Follow-up data

Study staff will administer follow-up surveys at 2 and 4 months after enrolment. Follow-up surveys will measure exposure to (and acceptability of) the interventions, changes in key demographics since enrolment (ie, marital status, number of children, employment, self-rated health), any adverse events since enrolment (ie, unwanted status disclosure, termination of relationship due to the intervention) and use of ART services. The location and specific time of the follow-up survey will be based on participant preference.

Medical chart reviews will be conducted to assess men’s engagement with ART services 6 months after study enrolment. Individuals without a medical chart outcome will be followed up in person and their health passport, a pocket medical record where providers record data during health visits, will be reviewed to collect the ART outcome. Men who cannot be reached or are lost to follow-up in any arm will be counted as failures for that specific ART outcome of interest: (re)initiation or 6-month retention.

### Patient and public involvement

Extensive formative work informed the development of the study protocol including in-depth interviews, focus group discussions and a systematic literature review. The study protocol and tools were presented to Ministry of Health, national stakeholders and implementing partners (see online supplemental file 2).

10.1136/bmjopen-2022-070896.supp2Supplementary data

### Cost data

The average cost per successful outcome (6-month retention) will be calculated and compared across arms incrementally. We will use micro-costing methods by creating an inventory of the resources used to achieve the observed study outcomes including: (1) standard counselling interactions (staff cadre, training received, duration of interaction and distance from facility travelled where applicable); (2) motivational interviewing interactions (staff cadre, training received, duration of interaction and distance from facility travelled where applicable); (3) provider interactions (staff cadre, training received, duration of interaction and distance from facility travelled where applicable); and (4) cost of reminder messages sent, when messages are delivered telephonically instead of in person. For each study patient, the quantity (number of units) of resources used will be determined. Costs will be measured from the healthcare provider perspective. Unit costs of resources, which are not human subject data, will be obtained from external suppliers and the health facilities’ finance and procurement records and multiplied by the resource usage data to provide an average cost per study patient in each study arm. A cost-effectiveness analysis will be conducted by dividing the incremental cost between two arms by the incremental effectiveness (number of people retained at 6 months) in the respective arms.

### Analysis plan

Data analysis will be conducted in R: A Language and Environment for Statistical Computing (R Foundation for Statistical Computing). We will use the Consolidated Standards of Reporting Trials standards for reporting trial outcomes.^42^ Using an intention-to-treat analysis, all randomised men will be included in the analysis of the primary outcome; men with missing outcomes due to loss to follow-up will be treated as outcome failures. We will calculate descriptive statistics, including mean, SD, range and frequency distributions for the demographic characteristics and study outcomes by study arm. The primary outcome and all other binary outcomes will be analysed by logistic regression models with age, marital status, healthcare facility and other key sociodemographic variables included as covariates. The intervention effects will be tested by Wald tests of the relevant regression parameters. The hypotheses of no difference between the stepped arm and the low/high-intensity arm will be rejected if the p value is smaller than 0.025 (Bonferroni adjustment). CIs for ORs comparing the stepped arm with the low-intensity and high-intensity arms with coverage probabilities 0.975 will be calculated by profile likelihood methods. Due to the Bonferroni adjustment, the simultaneous coverage probability of both intervals will be at least 0.95. To address the secondary objectives, more elaborate logistic regression models will be built for each of the binary outcomes with available individual-level, community-level and facility-level factors included as covariates in addition to the intervention status.

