### Study outcomes

The primary outcome is the proportion of men who are retained in ART care 6 months after (re-)engagement. Secondary outcomes include: (1) ART initiation; (2) adverse events experienced by men or their female partners (ie, unwanted disclosure, end of relationship or IPV; (3) intervention acceptability and (4) cost-effectiveness. ART retention outcomes will be measured through medical chart reviews, while secondary outcomes will be measured through self-reports. Process outcomes include: (1) the proportion of men who were successfully traced; (2) the proportion of eligible men who consented to participate; (3) men’s experience with the intervention and (4) the quality of the intervention.

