#### Sample size considerations

We powered the study to detect differences in 6-month retention between stepped and low-intensity arms, and the stepped and high-intensity arms. Based on pilot data, we assumed that 40% of men in the low-intensity arm, 60% in the stepped arm and 80% in the high-intensity arm will engage in ART and be retained at 6 months. Any man lost to follow-up will be treated as a failure for the outcome evaluation. With 181 men per arm and 20% loss to follow-up from the study in all arms, the power for detecting the specified differences between stepped and low-intensity arms and between stepped and high-intensity arms will be 0.8, with test level 0.025 after Bonferroni adjustment for two comparisons. We will have 0.99 power to detect specified differences between low-intensity and high-intensity arms. The calculation is based on asymptotic normality of log OR.^41^ We need to enrol and randomise 181 men per arm (a total of 543 men living with HIV).

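### The Wald test fixed for all binary outcomes loses most of its power for adverse events if a comparison arm has about 0–1% events, and its p value can then contradict the plan's own interval

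*Protocol article*

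**What the plan says.** The Analysis plan sets one method for all binary outcomes: "The primary outcome and all other binary outcomes will be analysed by logistic regression models with age, marital status, healthcare facility"; further sociodemographic covariates are to be added. It then fixes the test: "The intervention effects will be tested by Wald tests of the relevant regression parameters". The hypotheses of no difference between the stepped arm and each of the other two arms are rejected at p below 0.025. For the odds ratios of the same two comparisons it prescribes 97.5% confidence intervals by profile likelihood, so test and interval come from different methods. It also promises frequency distributions of the study outcomes by arm. For the secondary objectives, "more elaborate logistic regression models will be built for each of the binary outcomes", with individual-, community- and facility-level factors added.

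The Objectives section lists the presence of adverse events as a secondary objective, and Study outcomes lists "adverse events experienced by men or their female partners" as a secondary outcome. These are yes/no outcomes, so the Wald rule reads on them. The article gives no expected adverse-event rate and does not call these events rare. It names no other method for sparse outcomes.

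**The concern.** A Wald test divides the estimated log odds ratio by its standard error. When one arm has very few events, the standard error grows about as fast as the estimate, and the ratio stalls. With no events in one arm the estimate diverges, the standard error diverges faster, and the p value goes to about 1 however many events the other arm has. So the test is weakest in the clearest safety pattern: none in one arm and several in another.

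Adverse events are the trial's named safety outcome. A p value near 1, or just above 0.025, could be reported as no significant difference in partner violence or unwanted disclosure when that result comes from the test. The plan's own interval could exclude 1 on the same line of the table, and the article does not say which of the two governs.

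**Working it through.** **Inputs from the article.** 181 men per arm, allocated 1:1:1; 13 facilities; level 0.025 per comparison ("with test level 0.025 after Bonferroni adjustment for two comparisons"), taken as two-sided because sidedness is not stated, so the critical value is 2.241. Adverse-event rates are not given; 0–10% is assumed.

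**The plan's own figure.** There is none for harms, but the retention power confirms the sample size and test level. The section says "we assumed that 40% of men in the low-intensity arm, 60% in the stepped arm and 80% in the high-intensity arm" are retained, with 20% loss counted as failure, so the rates become 32%, 48% and 64%. Power = Φ(|log OR|/SE − 2.241), with SE² = [1/(p₁(1−p₁)) + 1/(p₂(1−p₂))]/181.
- Stepped v low: 0.674/0.218 − 2.241 = 0.849, power 0.802.
- Stepped v high: 0.655/0.215 − 2.241 = 0.811, power 0.791.

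Both agree with the stated 0.8. At these common rates the Wald approach works well.

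**Sparse 2×2 tables (unadjusted, 181 per arm).**
- 0 v 8 events: Fisher p = 0.007. The likelihood-ratio statistic is 2[8 ln 2 + 173 ln(173/181) − 354 ln(354/362)] = 11.27, p = 0.0008. The 97.5% profile interval for the odds ratio runs from about 2.8 with no finite upper limit. Wald p is about 1.
- 1 v 9 events: log OR = ln(9×180/172) = 2.243; SE = √(1 + 1/9 + 1/180 + 1/172) = 1.059; z = 2.12, Wald p = 0.034, not significant at 0.025. Fisher p = 0.020 and likelihood-ratio p = 0.006.
- With a single event in one arm, SE exceeds 1. The observed odds ratio must then exceed e^2.241 = 9.4 before Wald can reject. At 0.5–1%, the expected count per arm is only 0.9–1.8.

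**Simulated trials.** 3 × 181 men, 13 facilities as fixed indicators, age and marital status unrelated to harm, stepped v high, third arm at an intermediate rate. Entries are rejection rates at 0.025.

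| True rates | Wald, planned model | Wald, no facility terms | Firth (arm, age, marital status) | Fisher |
|---|---|---|---|---|
| 0 v 4% | 0% | 0% | 79% | 61% |
| 0.5 v 4% | 8% | 6% | 52% | 35% |
| 1 v 5% | 23% | 22% | 53% | 43% |
| 2 v 7% | 43% | – | 51% | 42% |

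Repeat runs of 400 to 600 trials moved individual entries by up to about 6 points and did not change the pattern. Dropping facility leaves Wald as weak as before, so the facility terms are not the cause.

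A separate run of 1,500 trials per scenario on stepped v low gave Wald v Fisher of 0.09 v 0.36 (4% v 0.5%), 0.23 v 0.39 (5% v 1%), 0.60 v 0.60 (8% v 2%) and 0.63 v 0.60 (10% v 3%). In every scenario with a true excess, Wald never rejected when either of these arms was empty. With 145 men per arm (20% without self-report), 5% v 0.5% gave 0.09 v 0.39.

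**Level with equal rates.** At 1–2% in all arms, Wald rejected about 0.3% of the time against a nominal 2.5%. Firth and Fisher stayed at or near or below the level, so their gain does not come from inflated error. The ordinary likelihood-ratio test in the full model, which the profile interval inverts, rejected about 4–5%.

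**Conflict between the two planned outputs.** The likelihood-ratio test rejected while Wald did not in about 51–53% of trials at 0.5 v 4%, and in about 32–33% at 1 v 5%.

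**The case against.** A reader might infer that the plan would hide a real excess of partner violence or disclosure. The document does not support that. Outcome frequencies are to be tabulated by arm, so 0 v 8 would be visible. The profile-likelihood interval does not collapse with an empty arm: in simulation it excludes 1 in about 91%, 60% and 54–56% of trials in the first three scenarios. What remains is one p value at odds with the table and interval beside it.

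A reader might also blame the 13 facilities. Facilities without events cannot have their own intercept estimated, but they drop out of the likelihood and the arm odds ratio is still estimable. The table bears this out.

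Rarity is not stated. The Objectives wording can be read as one composite of three events, which would be more frequent than each part. At 2% v 7% and above, Wald roughly matches Fisher. This stands, and it makes the point conditional.

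Finally, a sparse-data fallback could sit in an analysis plan that is not shown. That answers an omission, but here the article itself commits all binary outcomes to Wald tests, so a fallback elsewhere would contradict the published text.

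**Conclusion.** The point holds in a conditional form. The article fixes a Wald test for the adverse-event outcomes. If a comparison arm has about 0–1% events, that test loses most of its power: about 0%, 8% and 23% in the three sparse scenarios, against 79%, 52% and 53% for Firth and 61%, 35% and 43% for Fisher. With an empty arm its p value is near 1 whatever the other arm shows. By about 2% v 7% the deficit against Fisher is gone and against Firth it is about 8 points.

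The consequence is a misleading p value that can contradict the plan's own interval. Relying on the planned interval alone is not a full answer, because it runs somewhat above its level at 1–2% rates. The retention analysis is not affected.

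The figures rest on assumed event rates, a two-sided level, full follow-up of 181 per arm unless stated, and covariates unrelated to harm.

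**What to change.** In the Analysis plan, keep the Wald test for retention and ART (re)initiation. For each adverse-event outcome, name one of these in its place:

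- Firth penalised logistic regression with arm, and at most age and marital status, using the penalised-profile-likelihood test and 97.5% interval; or
- Fisher's exact test with an exact risk difference.

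With the Firth option, test and interval come from the same likelihood and agree; with the exact option, choose the interval method so that they do. State that the more elaborate covariate models will not be fitted to adverse events when events are few. Even a 5% rate gives only about 27 events (0.05 × 543) for at least 16 terms (2 arm, 12 facility, age, marital status), or about 1.7 per term.

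The cost is one paragraph; Firth regression is available in R, which the trial already uses. The small downside is that adverse-event contrasts would not be adjusted for facility.

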### Population

We will recruit men from 13 high-burden health facilities in Malawi, using medical chart reviews to identify men living with HIV who are not engaged in HIV care. Study facilities will vary by facility type (hospital/health centre), management (public/mission), location (rural/urban) and region (central/southern Malawi).

Eligibility criteria for men include: (1) ≥15 years of age; (2) live in facility catchment area; and (3) tested HIV positive and either (a) self-report having not yet initiated ART within 7 days of testing HIV positive, (b) initiated ART but are at risk of immediate default (ie, ≥7 days late for their 4-week ART refill appointment), or (c) initiated ART and attended their first refill appointment but later defaulted (ie, >28 days late to care). For those who never initiated ART and do not have proof of a confirmatory HIV test, study staff will offer an HIV self-test kit prior to enrolment, to confirm a positive HIV status. Those who choose to initiate ART will receive the standard Determine and Unigold confirmatory tests prior to ART initiation, following routine care.

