## Discussion

Studies have reported poorer outcomes for HIV testing, treatment initiation and treatment adherence in men compared with women^2^ for over a decade.^46 47^ Men are often portrayed as difficult, hard-to-reach and actively avoiding health facilities. In IDEaL, we aim to investigate whether men really are hard to reach or will men engage in care when services are offered in ways that are accessible to them and resonate with their needs, as growing evidence suggests.^17^ We propose testing a stepped intervention that increases in intensity over time against low-intensity and high-intensity interventions—all tailored to men—to identify the most cost-effective strategy to (re)initiate men in HIV treatment services in Malawi.

IDEaL is different from other ART engagement and re-engagement interventions in several important ways. First, we will enrol men living with HIV across the treatment cascade, including those who have never initiated ART, those who are at risk of immediate default after initiation and those who have been in care but subsequently defaulted. Formative research suggests that barriers to ART initiation and reinitiation may be similar^48^; however, most interventions focus specifically on either first-time initiation or re-engagement, but not both. Our study will assess if one overarching programme can improve men’s engagement across the treatment cascade, regardless of whether they are starting ART for the first time or returning to care after a period of disengagement. One overarching intervention may be more scalable than multiple, separate interventions across the cascade. Second, we tailor interventions to men’s unique needs and motivations, based on extensive formative work. While innovative interventions for men are underway,^25–27^ few have rigorously tested the impact of male-tailored interventions on ART engagement.^49^

Finally, we will test a stepped intervention that builds in intensity over time until men (re)initiate care. This approach allows men who are ready to (re)initiate to do so at minimal cost to the health system, while those who need additional support can receive more resource-intensive interventions to support their ART engagement.^31^ Stepped interventions have been effective in other settings and can address multiple barriers faced by the target population with minimal cost.^31 32^ Findings from IDEaL will provide crucial knowledge of how best men can be reached and can inform intervention scale-up.

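### The primary model's stated covariates leave out ART-engagement category at entry; adding it costs almost nothing, and the Discussion's cross-cascade aim needs an exploratory analysis by category or narrower wording

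*Protocol article*

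**What the plan says.** Under Population, a man who has tested HIV positive enters by one of three routes:

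- Route (a) is worded "self-report having not yet initiated ART within 7 days of testing HIV positive".
- Route (b) is worded "initiated ART but are at risk of immediate default", meaning at least 7 days late for the 4-week refill.
- Route (c) is worded "initiated ART and attended their first refill appointment but later defaulted", meaning more than 28 days late.

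Under Randomisation, allocation is 1:1:1 in blocks of 3 and 6 that depend on the men available at each facility. No stratum for route of entry is stated.

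Under Analysis plan, the primary outcome and the other binary outcomes are analysed with "logistic regression models with age, marital status, healthcare facility and other key sociodemographic variables included as covariates". The same section then turns to secondary questions and says that "more elaborate logistic regression models will be built for each of the binary outcomes with available individual-level, community-level and facility-level factors included as covariates". Study arm stays in those models too. No interaction is mentioned.

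The Discussion gives the mixed population as the first way in which the trial differs from others: "Our study will assess if one overarching programme can improve men’s engagement across the treatment cascade". The question is meant to cover men who are starting ART and men who are coming back to it.

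**The concern.** Two things do not fit together well.

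First, the article names the class of variables that the primary model adjusts for, and that class is sociodemographic apart from facility. Engagement category is clinical history and falls outside it. Yet the design itself creates this variable: it is settled at screening, before randomisation, and can hardly be missing, because a man without a category is not eligible. It is also plausibly related to 6-month retention. The Introduction reports that 30% to 40% of those who return to care have a repeat interruption within 6 months, but it gives no matching figure for first-time starters. If category is prognostic, leaving it out costs some precision and leaves chance differences in case mix between arms uncorrected.

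Second, a pooled arm effect is an average over the three routes. The same average could arise from a uniform effect or from an effect confined to one route. The Discussion's question about first-time starters and returners alike therefore needs estimates by category, and the Analysis plan section describes none.

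**Working it through.** **Inputs from Sample size considerations.** 181 men per arm; retention 40%, 60% and 80% (low, stepped, high); 20% loss to follow-up, counted as failure; test level 0.025 per comparison; asymptotic normality of the log odds ratio. The stated power is 0.8 for each comparison with the stepped arm. I took the test as two-sided, which the article does not state.

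**1. Reproducing the planned power.** With loss counted as failure the rates become 0.8 × (0.40, 0.60, 0.80) = 0.32, 0.48, 0.64. For stepped v low:

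- log OR = ln[(0.48/0.52)/(0.32/0.68)] = 0.674 (OR 1.96)
- SE = sqrt[1/(181×0.32×0.68) + 1/(181×0.48×0.52)] = 0.218
- power = Φ(0.674/0.218 − 2.241) = Φ(3.09 − 2.241) = 0.802

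Stepped v high gives 0.791. Both agree with the stated 0.8.

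**2. Power gained by adjusting for category.** Category shares and retention by category are not in the documents. I assume equal thirds, with retention at the mean minus d, the mean, and the mean plus d. The between-category variance is (2/3)d². The total variance at the average rate of the two arms, (0.32 + 0.48)/2 = 0.40, is 0.40 × 0.60 = 0.24. With r = (2/3)d²/0.24, power after adjustment is approximately Φ(3.09/√(1−r) − 2.241).

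| d | r | Power |
|---|---|---|
| 0.10 | 0.028 | 0.814 |
| 0.15 | 0.062 | 0.829 |
| 0.20 | 0.111 | 0.850 |

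A check on the logit scale, again with equal thirds and the marginal rates held at 0.32 and 0.48:

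| Logit shift between adjacent categories | Adjusted OR | Power |
|---|---|---|
| 0 | 1.96 | 0.80 |
| 0.5 | 2.01 | 0.82 |
| 1.0 | 2.18 | 0.85 |

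The two approaches agree: a gain of about 1 to 5 points.

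**3. Chance imbalance.** For one category holding a third of the men, the SD of the between-arm difference in its share is sqrt[2 × (1/3)(2/3)/181] = 0.0496, about 5 points. The SD of the resulting shift in the retention difference is sqrt[2 × (2/3)d²/181], which is 0.9 points at d = 0.10 and 1.7 points at d = 0.20. The planned difference is 48 − 32 = 16 points, with a standard error of sqrt[(0.32×0.68 + 0.48×0.52)/181] = 5.1 points. The unadjusted standard error already allows for this variation; adjustment removes it.

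**4. What an arm-by-category analysis could show.** Compare one category (share s) with the rest, at a two-sided level of 0.05, when the ratio of odds ratios is as large as the planned odds ratio (1.93 to 1.96). The interaction SE is sqrt[v/(181s) + v/(181(1−s))], with v = 1/(p₁q₁) + 1/(p₂q₂).

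| Share s | Power for the interaction | Ratio of ORs detectable with 80% power |
|---|---|---|
| 20% | 0.23 | 4.5–4.6 |
| one third | 0.30–0.31 | 3.6–3.7 |
| 50% | 0.33–0.34 | 3.3–3.4 |

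Within a single category, power for the planned effect at level 0.025 is about 0.19 at a 20% share, 0.32 at one third and 0.47 at one half.

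**The case against.** The strongest reply is that this is an article. Full covariate lists and subgroup analyses commonly sit in the full protocol or the SAP, which are not shown, and the phrase about other key variables signals a shortened list. For the arm-by-category analysis this largely stands: its absence here does not show that it is unplanned. It is weaker for the covariates, because the article states the class to be adjusted for, and engagement category lies outside that class.

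Second, choosing among valid covariate sets is partly preference. Randomisation protects the type I error, and the standard error already covers chance imbalance. This also stands. A reader might infer that the primary comparison is biased without category; it is not.

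Third, nothing in the article shows that category is strongly prognostic. A reader might suppose it to be among the best baseline predictors of retention, but no figure supports that. The Discussion says that barriers to starting and restarting may be similar. That remark concerns barriers and not retention rates, but it is the authors' reason for one programme. The gain in power is therefore conditional on the assumed spread, and the covariates already in the model may capture part of it.

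Fourth, some provision exists. The baseline survey records previous engagement with HIV services, the secondary models could take category as a main effect, and the nested studies look at factors associated with engagement within each arm. None of these estimates whether the arm effect is consistent across categories.

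**Conclusion.** The point holds as a low-to-moderate recommendation. A baseline variable that the design already fixes for every man lies outside the primary model's stated covariate class and is not a stated randomisation stratum. Using it would raise power for stepped v low from 0.80 to about 0.81–0.85 and would remove case-mix noise. Both figures rest on equal thirds, and the power range also on retention spreads of 10 to 20 points around the mean; the documents supply neither. If category is not prognostic, the gain is nil.

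The second part is narrower. A reader might take the Discussion to claim that the programme works across the whole cascade. It does not: it poses a question that the study will assess, and this is not among the stated objectives or outcomes. A pooled effect in a deliberately mixed population answers part of that question. It does not answer the part about first-time starters and returners alike, and at 543 men an interaction analysis could only be descriptive. A non-significant interaction would not show consistency.

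**What to change.** 1. In the Analysis plan, name ART-engagement category at screening (three levels, as in the eligibility criteria) as a fixed covariate in the primary logistic model. The cost is two parameters and no new data. The adjusted odds ratio is conditional on category and would be somewhat further from 1 than the unadjusted one (for example 2.01 to 2.18 against 1.96 under the assumptions above), so the report should say which is given.

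2. For the Discussion's aim, do one of the following:
   - pre-specify arm effects by category with confidence intervals and an arm-by-category interaction term, labelled exploratory, with a statement that a non-significant interaction is not evidence of a consistent effect. The cost is one table;
   - reword the aim as the average effect of one programme in a mixed population of first-time starters and returners. The cost is one sentence.

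If the full protocol or SAP already contains these items, only the article's wording needs to be brought into line. The specification should be fixed before outcome data by arm are seen, since a category table chosen afterwards would carry much less weight.

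### Holm's step-down rule would give more power than plain Bonferroni for the two primary comparisons, at the same familywise error and with no extra patients

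*Protocol article*

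**What the plan says.** The Sample size considerations section powers two comparisons, stepped against low and stepped against high, "with test level 0.025 after Bonferroni adjustment for two comparisons". It assumes retention at 6 months in "40% of men in the low-intensity arm, 60% in the stepped arm and 80% in the high-intensity arm". The stated power of 0.8 is given "With 181 men per arm and 20% loss to follow-up from the study in all arms", under the rule "Any man lost to follow-up will be treated as a failure for the outcome evaluation". The same section adds, for the third pair: "We will have 0.99 power to detect specified differences between low-intensity and high-intensity arms".

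The Analysis plan section fixes the decision rule for the two null hypotheses, stepped against low and stepped against high: each "will be rejected if the p value is smaller than 0.025 (Bonferroni adjustment". It pairs the two tests with two confidence intervals for the odds ratio at 97.5% coverage, so that joint coverage is at least 0.95. No step-down or closed procedure is mentioned. Low against high has no test level, interval or hypothesis there, and it is not part of the primary objective in the Objectives section.

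**The concern.** Single-step Bonferroni holds each test to 0.025 whatever the other test shows. Once one of two hypotheses has been rejected, only one remains, and strong familywise control at 0.05 allows it to be tested at the full 0.05. Holm's procedure does this. It needs no assumption about how the two tests are correlated, which matters here because both share the stepped arm.

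What is at stake is power already paid for. If both assumed effects are real, the fixed rule leaves some second comparisons unrejected although the familywise guarantee would permit rejection.

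**Working it through.** **Inputs** (Sample size considerations and Randomisation sections): 181 men per arm, 1:1:1 allocation; assumed retention 40% low, 60% stepped, 80% high; 20% loss in every arm, counted as failure; test level 0.025; normal approximation for the log odds ratio. Sidedness is not stated. Two-sided is assumed because the null is one of no difference, and because only that reading reproduces the stated power (one-sided gives 0.87 and 0.86).

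**Effective rates.** With loss as failure, each rate is multiplied by 0.8: 0.32, 0.48 and 0.64.

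**Reproducing the plan's power.** Power = Φ(|log OR|/SE − z), with SE² = the sum over the two arms of 1/[n p(1−p)] and z = 2.241 for two-sided 0.025.

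- Log odds: low −0.754, stepped −0.080, high 0.575.
- Variance terms: low 1/(181×0.32×0.68) = 0.02539; stepped 1/(181×0.48×0.52) = 0.02213; high 1/(181×0.64×0.36) = 0.02398.
- Stepped v low: 0.674/0.218 = 3.09; Φ(3.09 − 2.241) = 0.802.
- Stepped v high: 0.655/0.2147 = 3.05; Φ(3.05 − 2.241) = 0.791.
- Low v high: 1.329/0.222 = 5.98; power above 0.999.

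The stated 0.8 reproduces, and the stated 0.99 is met.

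**Comparing the rules.** One million trials per scenario were simulated with binomial counts and unadjusted two-sided Wald tests on the log odds ratio.

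At 32/48/64%, 181 per arm:

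| Rule | Stepped v low | Stepped v high | Both | At least one |
|---|---|---|---|---|
| Bonferroni, 0.025 each | 0.811 | 0.792 | 0.611 | 0.991 |
| Holm, 0.025 then 0.05 | 0.870 | 0.864 | 0.743 | 0.991 |

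The rows are consistent: P(both) = the sum of the two powers − P(at least one). For Bonferroni, 0.811 + 0.792 − 0.991 = 0.612 (0.611 before rounding). For Holm, 0.870 + 0.864 − 0.991 = 0.743. The last column cannot change, because Holm's first step is the Bonferroni test.

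**Error control and limits of the gain.**

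- All three arms equal at 48%: the chance of any false rejection among the two tests is 0.044 under either rule.
- Stepped equal to low (48/48/64%): power for stepped v high moves only from 0.792 to 0.794. The false rejection rate for stepped v low rises from 0.024 to 0.043, still below 0.05.
- Stepped equal to high (32/48/48%): power for stepped v low moves only from 0.811 to 0.813. The false rejection rate for stepped v high rises from 0.024 to 0.043.

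**Equivalent in patients.** By the same simulation, Bonferroni reaches about the same chance of rejecting both at 210 to 215 men per arm (0.736 and 0.745). That is 29 to 34 more per arm, or 87 to 102 in total.

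**The case against.** The strongest reply is that nothing is broken. The two sections agree on two named hypotheses at 0.025 each, the sample size follows from that rule, and the trial has its stated power under it. This stands, and it is why the point is an improvement and not a correction.

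The second reply is that Bonferroni was paired with simultaneous intervals on purpose, so that test and interval agree apart from small differences between Wald tests and profile likelihood. This also stands as a real cost. The whole rise in the chance of rejecting both (0.743 − 0.611, about 0.13) comes from trials where the second p value lies between 0.025 and 0.05. In essentially all of those the reported 97.5% interval includes 1. Whether that is acceptable is for the sponsor to judge, but familywise control of the decisions is unaffected.

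The third reply is that the gain depends on the scenario. That is correct: if only one effect is real, Holm adds almost nothing. It also never loses power relative to the present rule.

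A reader might go further and infer that the trial is underpowered because the chance of rejecting both is 0.61. The protocol does not support this. It powers each comparison separately and nowhere requires both to succeed. If success did require both, each could be tested at 0.05 with no adjustment for that joint claim, giving a joint power of about 0.745.

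**Conclusion.** The point holds as a cheap improvement. The fixed 0.025 rule is valid and delivers the stated power. Holm gives the same familywise guarantee and is never less powerful. At the design assumptions it adds about 6 to 7 percentage points of power per comparison and 13 points to the chance of rejecting both, with no added patients. The gain needs both effects to be real, and the chance of at least one rejection does not change. The figures assume two-sided tests and unadjusted Wald statistics; covariates and facility effects are not modelled.

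A reader might also infer from the power sentence for low against high that familywise error is inflated by a third test outside the adjusted family. The documents do not support that. The comparison is absent from the primary objective and from the tested hypotheses, and no level is assigned to it. An error rate computed over three tests would describe a plan that the protocol does not contain.

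**What to change.** In the Analysis plan section, replace the decision rule with Holm's: compare the smaller of the two p values with 0.025 and, if that hypothesis is rejected, compare the other with 0.05; if the first is not rejected, reject neither. Keep the two 97.5% intervals as the simultaneous intervals and keep 181 men per arm. Add one sentence saying that the second hypothesis may be rejected while its 97.5% interval still includes 1, because the decision and the interval then rest on different procedures. In the Sample size considerations section, note that 0.025 is the level used for sizing and is conservative for the Holm rule.

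The cost is a few sentences and the possible mismatch between test and interval. The change should be made and dated before outcomes are compared between arms.

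Only if the sponsor wants a confirmatory claim on low against high is a further step needed. An option then is the closed test for three arms: a 2-degree-of-freedom test of equality at 0.05, followed by each pair at 0.05. In the same simulation it gives 0.875 and 0.869 for the two stepped comparisons and above 0.999 for low against high, with a familywise error of 0.049 when all arms are equal. Otherwise low against high can stay outside the family.
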